## Abstract

**Objective:**

This study innovatively employs transcutaneous auricular vagus nerve stimulation (taVNS), a non-invasive physical therapy, to intervene in elderly patients with chronic insomnia (CI) comorbid with functional dyspepsia (FD). Through systematic investigation of the molecular mechanisms underlying vagus nerve pathway regulation in ameliorating intestinal inflammatory microenvironment and modulating central neurotransmitter homeostasis, this research aims to provide a novel, neuromodulation-based precision therapeutic approach characterized by favorable safety and tolerability for integrated management of geriatric comorbidities.

**Methods/design:**

This double-blind randomized controlled trial will enroll 60 elderly patients (60–85 years) meeting ICSD-3 criteria for CI and Rome IV criteria for FD. Using block randomization with computer-generated sequences, eligible participants will be allocated 1:1 to either active taVNS group (*n* = 30) or sham control group (*n* = 30). The CFDA-certified transcutaneous vagus nerve stimulator (Model tVNS501, Reach Medical, China; Registration No. SuXieZhun20212090050) will be positioned at standardized anatomical sites: the concha cymba (the inferior margin of the intersection between the superior and inferior crura of the antihelix within the cymba conchae), electrical stimulation will deliver with fixed parameters (frequency: 80 Hz, pulse width: 100 μs, pulse 40–60s). The active group will receive validated taVNS parameters, while the sham group will undergo identical procedures without electrical output. Interventions will be administered 30 min per session, 5 sessions weekly for 3 consecutive weeks. Primary endpoints include changes in Pittsburgh Sleep Quality Index (PSQI) and Nepean Dyspepsia Symptom Index (NDSI) at week 3. Secondary outcomes encompass Insomnia Severity Index (ISI), 36-Item Short Form Survey (SF-36), and serum biomarkers (pro-inflammatory cytokines IL-1*β*, IL-4, IL-6, TNF-*α*, hs-CRP, TGF-β; neurotransmitters Dopamine (DA), serotonin (5-hydroxytryptamine, 5-HT), norepinephrine (NE), Glutamate (Glu), *γ*-aminobutyric acid (GABA)). Safety profiles will be systematically evaluated using CTCAE v5.0 criteria, with all adverse events documented throughout the study.

**Discussion:**

This study mitigate the adverse effects associated with the significant side effects of oral medications in elderly patients with CI comorbid with FD. It seeks to scientifically validate the clinical efficacy of taVNS therapy, elucidate its underlying anti-inflammatory and neuromodulatory mechanisms, and establish a multimodal evidence chain integrating “efficacy-inflammation-neuromodulation.” By doing so, this research provides a novel, convenient, scientifically validated, effective, and safe non-pharmacological therapeutic approach for elderly patients with CI and FD, it offers innovative insights and methodologies for the development of pharmaceuticals, medical devices, and related products.

## Background

1

According to the 2022 Statistical Bulletin of National Economic and Social Development released by National Bureau of Statistics of China, by the end of 2022, the population aged 60 years and above in China had reached 280 million, accounting for 19.8% of the total population, among which 210 million were aged 65 years and above, representing 14.9% of the population. The “14th Five-Year Plan” for Healthy Aging issued by National Health Commission of the PRC highlights the concerning health status of the elderly population, with over 78% suffering from at least one chronic disease. This necessitates a shift in elderly healthcare services from a single-disease model to a multi-morbidity management model. The Blue Book of Aging Society: Report on Aging Society Development (2022) published by the China Research Center on Aging reveals that over 180 million elderly individuals in China are affected by chronic diseases, with an average duration of life with chronic diseases of 9.1 years among those aged 60 and above. Moreover, two-thirds of individuals aged 65 and above suffer from multiple coexisting conditions.

In terms of disease prevalence, chronic diseases are highly prevalent among the elderly, and more than half experience poor sleep quality. Studies indicate (1–6) that approximately 10–30% of adults worldwide suffer from insomnia, with the prevalence among the elderly (≥65 years) ranging from 30 to 50%. In China, the incidence of insomnia has reached 38.2%, affecting over 300 million individuals, and the prevalence of sleep disorders among the elderly is 46.0%.

The expert consensus on the diagnosis and treatment of functional dyspepsia in the elderly reports that the global prevalence of dyspepsia is approximately 20%, with rates in Asia ranging from 8 to 23%, and the prevalence among Chinese elderly ranging from 18 to 35% (7). CI comorbid with FD is a highly prevalent clinical manifestation. Research shows (8) that up to 79.48% of insomnia patients exhibit gastrointestinal symptoms, while nearly 70% of elderly individuals with dyspepsia experience comorbid insomnia. Dyspepsia and insomnia often coexist, and sleep quality is closely associated with the severity and prognosis of dyspepsia. Patients with dyspepsia and impaired sleep quality tend to exhibit more severe symptoms and poorer prognoses (9, 10).

Currently, pharmacological treatments for CI in the elderly are associated with systemic risks. Studies have shown (11–14) that the risk of dependence on benzodiazepines is 34.7% (OR = 3.2, 95%CI 2.1–4.9), and the incidence of withdrawal syndrome after discontinuation is 28.4% (RR = 2.8). Additionally, a significant dose ineffectiveness threshold effect has been observed, necessitating off-label dosing in some patients, while 12.7% of patients exhibit a decline in estimated glomerular filtration rate (eGFR), and the incidence of hepatorenal toxicity is ≥30%. The treatment of FD lacks targeted therapies and effective drugs, with proton pump inhibitors (PPIs) showing a clinical response rate of only 38.2% (95%CI 32.7–44.1), and long-term use of prokinetic agents increases the risk of QT interval prolongation (HR = 1.68) (15, 16).

When CI and FD coexist, the risk of drug interactions increases by 71% (*p* < 0.001) (17), and the cost-effectiveness ratio of conventional therapies is as high as $152,300 per quality-adjusted life year (QALY) (18). Therefore, there is an urgent need for reliable, safe, cost-effective, and efficient clinical treatment options for elderly patients with CI comorbid with FD. In this context, taVNS emerges as a novel therapeutic approach, offering a potential innovative solution for this patient population.

This study will systematically evaluate the clinical efficacy of transcutaneous auricular vagus nerve stimulation (taVNS) in elderly patients with CI comorbid with FD. By analyzing dynamic fluctuations in inflammatory cytokines and neurotransmitters, we will objectively validate the clinical effectiveness of taVNS in geriatric comorbidity management for the first time. The investigation will further elucidate the vagus nerve-mediated regulatory mechanism of duodenal mucosal inflammation and establish a novel non-pharmacological intervention characterized by precision targeting, high safety profile, and enhanced therapeutic compliance, which will provide a theoretical foundation for developing neuromodulation-based integrated therapeutic strategies for elderly patients with multimorbidity management.

## Methods/design

2

### Settings and subjects

2.1

This randomized controlled trial (RCT) was conducted at the Sichuan integrative medicine hospital (Chengdu, Sichuan, China). The study protocol (Version 2.0, dated March 14, 2024) strictly adhered to the ethical principles of the Declaration of Helsinki and was approved by the Clinical Research Ethics Committee of the Sichuan Provincial Hospital of Integrated Traditional Chinese and Western Medicine (Approval No.: KY-2024-001; Date: March 18, 2024).

In accordance with the International Standards for Clinical Trial Registration (ICTRP), the research team prospectively registered the trial at the Chinese Clinical Trial Registry on February 2, 2024 (Website: www.chictr.org.cn; Registration No.: ChiCTR2400080630).

In compliance with ethical requirements, researchers provided detailed explanations of the study objectives, procedures, and potential risks to all participants. Informed consent was obtained from each participant after ensuring their full understanding of the study, and participants retained the right to withdraw unconditionally at any time. The first participant was formally enrolled on July 26, 2024, marking the commencement of the study’s implementation phase.

### Diagnostic criteria

2.2

Participants must meet both international diagnostic standards: Chronic Insomnia (ICSD-3) (19) and Functional Dyspepsia (Rome IV) (20).

### Inclusion criteria

2.3

*Age and gender*: Participants aged between 60 and 85 years, regardless of gender.

*Clinical presentation*: Patients exhibiting a chronic, recurrent condition that meets the diagnostic criteria, with no evidence of structural diseases that could explain the aforementioned symptoms.

*Diagnostic tests*: Completion of electronic gastroscopy or upper gastrointestinal radiography, blood biochemistry, and stool routine tests within the past year, with results confirming the absence of structural abnormalities, ensuring the exclusion of other diseases causing dyspeptic symptoms, and ruling out organic digestive system diseases, metabolic or systemic diseases. There should be no evidence of chronic gastritis with erosion, ulcers, tumors, or other organic lesions.

*Medication and MRI contraindications*: No intake of gastrointestinal motility drugs, antacids, or sleeping pills within the past week. Absence of metal implants or claustrophobia, which are contraindications for MRI.

*Informed consent*: Participation must be based on genuine personal willingness, adherence to the clinical trial design, and the signing of an informed consent form.

### Exclusion criteria

2.4

*Systemic diseases*: Patients with severe psychiatric disorders, severe cardiovascular or cerebrovascular diseases, hepatic or renal dysfunction, digestive dysfunction, coagulation disorders, or other severe systemic diseases.

*Medical history*: Individuals with a history of gastrointestinal surgery, psychiatric disorders, alcohol abuse, or drug abuse. Patients with overlapping syndromes such as Gastroesophageal Reflux Disease (GERD) or Irritable Bowel Syndrome (IBS), or those with current *Helicobacter pylori* infection.

*Systemic or environmental factors*: Patients experiencing insomnia or dyspepsia caused by systemic conditions such as pain, fever, cough, surgery, trauma, or external environmental factors.

*Ear skin conditions*: Patients with skin conditions in the ear stimulation area that may affect conductivity, including allergies, abrasions, ulcers, edema, neoplasms, scars, inflammation, or papules.

### Sample size estimation

2.5

Based on existing RCT literature, the efficacy rate of taVNS in treating elderly patients with CI ranges from 73.3 to 93.3% (21, 22), while its efficacy in FD reaches 92.3% (3). Building upon our preliminary exploratory clinical study involving 10 cases, we observed an 80.0% efficacy rate (*p* < 0.01) for taVNS in treating elderly patients with CI comorbid with FD, demonstrating significant clinical effectiveness.

This study employed a superiority trial design and utilized PASS 2021 software (NCSS LLC, Kaysville, USA) for prospective sample size estimation. Based on clinical data reported in reference (23), with anticipated efficacy rates of 20% in the sham stimulation group and 70% in the active stimulation group, we conducted a two-independent proportion *z*-test analysis with the following parameters: type I error probability *α* = 0.05, statistical power 1-*β* = 0.99, and 1:1 allocation ratio. Through Monte Carlo simulation validation, the minimum theoretical sample size was calculated as 28 participants per group.

In accordance with CONSORT Statement guidelines regarding dropout rates and considering our institutional clinical practice experience with anticipated 5–10% dropout rates, we ultimately determined to enroll 30 participants per group (total *N* = 60). This sample size enables detection of a Cohen’s *h* effect size of 0.99 (Power = 0.991, 95% CI 0.89–1.07), satisfying the statistical power requirements for superiority trials.

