After de-identified data underwent ETL (Extract-Transform-Load) processing for standardization, the standardized data were imported into statistical software for further analysis. Measurement data were expressed as Mean ± SD. Differences among groups were analyzed by Student *t* test or one-way ANOVA, SNK or LSD method was used for multiple comparison. Qualitative data were described as percentages and analyzed using Chi-square (*χ*^2^) test or Fisher’s exact test as indicated. The *p*-value reported was two-sided and value of less than 0.05 was considered statistically significant. All analyses were performed using the SPSS software (Version 20.0, SPSS Inc., USA).

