This randomized double-blind sham-controlled trial comprised an active group receiving taVNS at the concha cymba (frequency: 80 Hz, pulse width: 100 μs, pulse 40–60s) for 30 min per session, 5 sessions weekly for 3 consecutive weeks, alongside the sham group undergoes identical procedures with non-active electrodes. Primary endpoints included variations in the PSQI and NDSI, with secondary outcomes encompassing ISI, SF-36, serum biomarkers (pro-inflammatory cytokines IL-1*β*, IL-4, IL-6, TNF-*α*, hs-CRP, TGF-β) and neurotransmitters (DA, 5-HT, NE, Glu, GABA). Should the trial demonstrate statistical superiority of taVNS over sham in both symptom domains, it will not only elucidate the neuroimmune axis mechanism underlying comorbid CI with FD in elderly patients (e.g., vagus nerve-mediated duodenal mucosal inflammatory regulation), but also propose a novel non-pharmacological intervention characterized by precision targeting, elevated safety, and optimal adherence, thereby establishing a neuromodulation-based integrative therapeutic strategy for geriatric comorbidity management.

This study acknowledges limitations inherent to its exploratory design. The modest sample size reflects both the prospective nature of the trial and stringent inclusion criteria for CI comorbid with FD. Although preliminary clinical evidence suggests the therapeutic efficacy of high-frequency taVNS, the absence of prior literature supporting this intervention introduces potential bias and elevates uncertainty in evidence quality. Current taVNS protocols lack expert consensus regarding optimal stimulation parameters (frequency, intensity, site), and resource constraints precluded comparative effectiveness analyses across parameter combinations. Furthermore, the absence of objective neuroimaging or electroencephalographic biomarkers in outcome measures may introduce measurement bias. These limitations will be systematically addressed in subsequent validation studies.

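### The 99% power claim rests on an undefined binary efficacy rate that is not an endpoint, so power for the two primary scale comparisons (PSQI and NDSI) is not established

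*Protocol article*

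**What the plan says.** Section 2.5 plans on "anticipated efficacy rates of 20% in the sham stimulation group and 70% in the active stimulation group" and sizes the trial with a test of proportions: "we conducted a two-independent proportion *z*-test analysis". The settings are "type I error probability *α* = 0.05" and "statistical power 1-*β* = 0.99, and 1:1 allocation ratio". The result is 28 per group, raised to 30 for an expected 5–10% dropout, with power of 0.991 stated for the final size. The section does not say what counts as a response.

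The abstract defines the primary question differently: "Primary endpoints include changes in Pittsburgh Sleep Quality Index (PSQI) and Nepean Dyspepsia Symptom Index (NDSI) at week 3". The Discussion likewise describes variations in the two scores. Section 2.8.2 attaches one cut-off to each scale (PSQI change of at least 3 points; NDSI reduction of at least 30%). It does not name either as an endpoint, combine them, or connect them to the 70% and 20%.

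Section 2.8.5 compares measurement data between groups by Student t test or ANOVA, with p-values "two-sided and value of less than 0.05 was considered statistically significant". The nearest thing to a success rule is a conditional clause in the Discussion: "Should the trial demonstrate statistical superiority of taVNS over sham in both symptom domains".

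**The concern.** A power statement describes one outcome, one test and one assumed effect. Here the outcome and test in 2.5 (a proportion, by z-test) are not those of the primary endpoints (changes on two scales, compared as means). The article supplies no bridge between them: no response definition, no SD, no mean difference. A reader told that the trial has 99% power would take a null result on PSQI or NDSI as strong evidence against an effect, and the document gives no ground for that.

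There are also two primary scales, and 2.5 computes power for a single outcome. If the claim is to rest on both domains, as the Discussion suggests, the relevant figure is the probability that both comparisons succeed. That figure is not given.

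**Working it through.** **1. The plan's own figure.** Inputs from 2.5: 20% versus 70%, alpha 0.05, power 0.99, 1:1. Two-sidedness is taken from 2.8.5, because 2.5 does not state it. Unpooled two-proportion z-test:

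n = (1.960 + 2.326)² × (0.2×0.8 + 0.7×0.3) / 0.5² = 18.37 × 0.37 / 0.25 = 27.19, rounded up to 28.

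This matches. At 30 per group the power is 0.994 (unpooled) or 0.987 (pooled), consistent with the stated 0.991. The arithmetic is not the problem.

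**2. What 30 per arm buys on a scale.** Two-sided t-test at 0.05, noncentral t with 2n − 2 degrees of freedom and noncentrality d√(n/2), where d is the between-group difference in SD units. The 27 per arm is 30 × 0.90, the upper end of the stated dropout.

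| Power for one scale | d at 30 per arm | d at 27 per arm |
|---|---|---|
| 80% | 0.74 | 0.78 |
| 90% | 0.85 | 0.90 |
| 99% | 1.13 | 1.19 |

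**3. Power at assumed effects.** The document gives no SD or mean difference, so every d below is an assumption.

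| Assumed d on each scale | Per arm | One scale | Both scales, correlation 0 to 0.5 |
|---|---|---|---|
| 0.8 | 30 | 86% | 74% to 77% |
| 0.8 | 27 | 82% | 68% to 72% |

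At correlation 0 the joint figure is the square of the single-scale power: 0.861² = 0.741 and 0.822² = 0.676. The figures at correlation 0.5 come from simulating the two t-tests together.

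**4. The plan's own effect carried over to a scale.** Suppose 70% versus 20% held on each scale, through a common cut-off on normally distributed scores with equal SDs. Then d = probit(0.70) − probit(0.20) = 0.524 + 0.842 = 1.37. The t-test power is then 0.999 at 30 per arm and 0.998 at 27. Even with independent scales, joint power is about 0.999 and 0.997.

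**5. Result.** Depending on what the efficacy rate means, the same N = 60 gives joint power from about 68% (0.8 SD, 27 per arm, correlation 0) to above 99% (1.37 SD). The document does not allow a choice between these.

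**The case against.** The strongest reply is that moving from a proportion to a mean need not cost power. Step 4 shows that, on the only planning effect in the document, a t-test on the full score would do at least as well as the z-test. If the rate instead meant responding on both scales, the implied difference per scale would still be 1.11 to 1.30 SD (correlation 0 to 0.7), with power of 0.980 to 0.997 per scale at 27 per arm. This stands against any claim that the trial is underpowered. The 0.8 SD figures illustrate how far power depends on the effect; they do not estimate it. The reply does not rescue the 99% claim, because the article never says that the rate applies to either scale, or to both.

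A second reply is that the cut-offs in 2.8.2 sit under the primary outcomes and that 2.8.5 provides chi-square tests for qualitative data. A responder comparison would therefore fit the text. It would also be too strong to say that the t-test is expressly assigned to the primaries: 2.8.5 speaks of measurement data generally, and 2.11.2 adds adjusted regression. All this is fair, but a responder comparison is still not named as an endpoint.

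A reader might also infer that type I error is nearly doubled. With each scale tested at 0.05 and either one sufficient, the family-wise error would be 1 − 0.95² = 9.75% at correlation 0 and 9.1% at 0.5. The document does not state that rule. The Discussion points to both domains, in which case there is no inflation, and a multiplicity rule may sit in an analysis plan that is not shown. The wording "one-way ANOVA, SNK or LSD method was used for multiple comparison" does not help either way, since it concerns comparisons among groups rather than two endpoints.

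**Conclusion.** The point holds as a mismatch within the document. The 99% power belongs to an undefined binary outcome that is not an endpoint, and nothing links it to the PSQI and NDSI comparisons that are primary. It also covers one outcome where the Discussion envisages two. The sample-size arithmetic itself is sound.

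The documents do not show that N = 60 is too small. Actual power is unknown, because no SD or mean difference is given. The detectable differences in step 2 depend only on the t-test, two-sided 0.05 and the numbers per arm. The power figures in steps 3 and 4 depend on assumed effects and correlations and, in step 4, on a normal model with equal SDs and a common cut-off. Inflated type I error is not part of the conclusion.

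**What to change.** Keep N = 60.

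- **Section 2.5:** replace the 99% claim with the detectable standardised difference for each primary scale and the joint power for both, at 30 and 27 per arm. State the assumed effect and correlation, and give any SD used with its source.
- **Section 2.8.2:** carry over the rule implied in the Discussion. Week-3 PSQI and NDSI are co-primary, each tested at two-sided 0.05, and success requires both. No alpha split is then needed.
- **Responder rates:** define them by the cut-offs already in 2.8.2 and report them as secondary outcomes. If the 70% and 20% are kept as background, say which definition they refer to.

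The cost is a rewritten 2.5 and a few sentences in 2.8.2, with no extra participants and no change to the primary measures. Enrolment began in July 2024, so the clarification should be dated and made before unblinding. The stated power may become less favourable, depending on the effect that the sponsor can justify.

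### Section 2.5 says simulation validated 28 per group as the minimum for 99% power; under the plan's two-sided 0.05 rule, actual power at 28 is about 98%, a small shortfall

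*Protocol article*

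**What the plan says.** Section 2.5 (Sample size estimation) of the protocol article starts from "anticipated efficacy rates of 20% in the sham stimulation group and 70% in the active stimulation group". It names a "two-independent proportion *z*-test analysis", run in PASS 2021 with 1:1 allocation, "type I error probability *α* = 0.05" and "statistical power 1-*β* = 0.99". It then reports: "Through Monte Carlo simulation validation, the minimum theoretical sample size was calculated as 28 participants per group". Enrolment is set at 30 per group, 60 in total, to allow for losses. The section does not say whether alpha is one- or two-sided, or whether the z-test uses pooled or unpooled variance.

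Section 2.8.5 (Statistical analysis) settles the sidedness of the analysis: the p-"value reported was two-sided and value of less than 0.05 was considered statistically significant". For proportions it says: "Qualitative data were described as percentages and analyzed using Chi-square", with Fisher's exact test as the alternative where indicated.

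**The concern.** A sample size formula and a simulation answer different questions. The formula rests on a normal approximation. A simulation draws the binomial data, applies the test and counts rejections, so it shows the power the test really has. With about 30 per group and a target as high as 0.99, the two can differ by a point or more.

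The protocol says that simulation confirmed 28 as the smallest size giving 0.99. If actual power at 28 is below 0.99 for the tests the plan uses, that sentence reports a check that the plan's own inputs do not bear out. What is at stake is the accuracy of the stated power and of the claimed verification. The adequacy of 60 participants is not in question here.

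**Working it through.** **Inputs.** From section 2.5: p1 = 0.70, p2 = 0.20, difference 0.50, alpha 0.05, power 0.99, 1:1 allocation. From section 2.8.5: two-sided testing, so z = 1.960 for alpha; z = 2.326 for power 0.99. The mean rate is (0.70 + 0.20)/2 = 0.45.

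**Step 1: reproduce 28.** With unpooled variance,

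n = (1.960 + 2.326)² × (0.70×0.30 + 0.20×0.80) / 0.50² = (1.960 + 2.326)² × 0.37 / 0.25 = 27.19, rounded up to **28**.

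By this approximation, power is 0.992 at 28 and 0.994 at 30. The stated figure is reproduced.

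**Step 2: the formula for the chi-square test.** Without continuity correction, the chi-square test for two proportions is the pooled z-test:

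n = (1.960 × √(2×0.45×0.55) + 2.326 × √0.37)² / 0.25 = 31.23, rounded up to **32**.

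So even by formula, the test named in section 2.8.5 needs 32 for 0.99.

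**Step 3: actual power.** For each n, sum Binomial(x; n, 0.70) × Binomial(y; n, 0.20) over all pairs (x, y) that the two-sided 0.05 test rejects. This is the value a simulation converges to.

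| n per group | unpooled z | pooled z / chi-square | Fisher's exact |
|---|---|---|---|
| 28 | 0.981 | 0.976 | 0.956 |
| 30 (no losses) | 0.9855 | 0.9853 | 0.971 |
| 31 | 0.9888 | 0.9887 | 0.978 |
| 32 | 0.9914 | 0.9913 | 0.983 |

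A simulation of 1,000,000 trials with the two-sided pooled z-test gave 0.976 at 28 and 0.985 at 30, in agreement with the enumeration.

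**Step 4: size of the gap.** At 28, 0.990 − 0.981 = 0.009 and 0.990 − 0.976 = 0.014, so the shortfall is 0.9 to 1.4 points. The type II error is 1.9% to 2.4% instead of 1%. At 30, 0.990 − 0.985 = 0.005, half a point. Both z-tests first reach 0.99 at 32 per group.

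**Step 5: one-sided alpha, since section 2.5 does not exclude it.** One-sided formulas give 24 (unpooled), 27 (pooled), 28 (unpooled with continuity correction, 27.19), 29 (arcsine) and 31 (pooled with continuity correction). Actual one-sided power at 28 is 0.993 for the unpooled z-test and 0.989 for the pooled; at 30 both are 0.993. The unpooled test already passes 0.99 at 27 (0.9924, against 0.9899 at 26), and the pooled test first does so at 29 (0.9912).

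**The case against.** The strongest reply is that nothing was miscalculated. Section 2.5 names a z-test, and a standard form of it returns 28 from the stated inputs. This stands: 28 is a valid normal-approximation result, and calling it an arithmetic slip would be wrong. What the reply does not cover is the added statement that simulation confirmed it.

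A second reply is that section 2.5 leaves sidedness open. This stands in part. A reader might infer that 28 cannot come from a one-sided alpha, or that no version of the test reaches 0.99 at 28. Neither is supported: the one-sided unpooled formula with continuity correction also gives 28, and the one-sided unpooled z-test has actual power 0.993 there. But section 2.8.5 fixes two-sided p-values at 0.05, and power should be quoted for the test that will be run.

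Third, the Fisher figure of 0.956 invites a more alarming reading. Section 2.8.5 offers Fisher only where indicated. With 28 per group and a mean rate of 45%, the expected counts are 28 × 0.45 = 12.6 and 28 × 0.55 = 15.4, so by the usual small-count convention the chi-square test would be used. Fisher's values belong in the text only as what would follow if it were chosen.

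Fourth, the simulation itself is not shown: the article does not say which statistic was simulated, how many runs were made or what power came out. This also stands. The supportable conclusion is that a two-sided simulation of the named test at these rates would give about 98%, not that no simulation was done.

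**Conclusion.** The point holds in a limited form and is minor. Under the two-sided 0.05 rule of section 2.8.5 and the assumed 70% against 20%, simulation would not confirm 28 per group as the minimum for 0.99. Actual power is about 98% at 28 and about 98.5% at 30 with no losses, and 0.99 is first reached at 32.

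A reader might go on to conclude that the trial is underpowered. The figures do not support that: on the assumed rates, power at 28 exceeds 95% for every test in the table and is close to 98% for the one likely to be used. The result rests on the assumed response rates, on two-sided testing, and on an uncorrected chi-square test. It says nothing about whether those rates are realistic, about the effect-size sentence in section 2.5, or about the allowance for dropout.

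**What to change.** Keep 60 participants and edit section 2.5:

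- State that alpha is two-sided and which variance form the z-test used to obtain 28.
- Restate the power for the planned analysis, for example: with response rates of 70% and 20% and a two-sided chi-square test at 0.05, actual power is about 98% with 28 per group and about 98.5% with 30 per group and no losses. If Fisher's exact test is kept as a real option, add 95.6% and 97.1%.
- Delete the claim that simulation validated 28 as the minimum for 0.99, or report what was simulated: the test, its sidedness, the number of runs and the power obtained.

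The cost is one or two sentences. No patients are added and neither the design nor the analysis changes; the stated power becomes slightly less favourable.

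### The stated Cohen's h of 0.99, power of 0.991 and interval of 0.89–1.07 do not fit together, and 30 per group does not cover 10% dropout

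*Protocol article*

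**What the plan says.** Section 2.5 of the protocol article (Sample size estimation) sizes the trial on "anticipated efficacy rates of 20% in the sham stimulation group and 70% in the active stimulation group". The method is a "two-independent proportion *z*-test analysis with the following parameters": "type I error probability *α* = 0.05", power "0.99, and 1:1 allocation ratio". The section does not say whether alpha is one- or two-sided, or which form of the z-test was used. Section 2.8.5 (Statistical analysis) makes reported p-values two-sided, and there a "value of less than 0.05 was considered statistically significant".

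The result is that "the minimum theoretical sample size was calculated as 28 participants per group". The protocol then allows for "anticipated 5–10% dropout rates" and settles on 30 per group, 60 in all.

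The closing sentence says this size can detect a Cohen's h "effect size of 0.99 (Power = 0.991, 95% CI 0.89–1.07", and concludes that the power needed for a superiority trial is met. It does not say what the interval refers to.

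**The concern.** Cohen's h is fixed by the two response rates alone. Sample size, sidedness and choice of test play no part in it. If the stated h does not match 70% and 20%, the closing sentence describes an effect other than the one the trial was sized for. A power attached to that h can then be checked directly, and so can an interval attached to either quantity.

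This sentence is the stated ground for calling the sample size adequate. As it stands, a reader cannot tell which effect 30 per group is meant to detect, or with what power. Separately, the step from 28 to 30 looks small against a dropout allowance that runs up to 10%.

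**Working it through.** **Inputs** (all from section 2.5 unless noted): p1 = 0.70, p2 = 0.20, alpha = 0.05, target power 0.99, 1:1 allocation, minimum 28 per group, 30 enrolled per group, dropout 5–10%. Two-sided testing is taken from section 2.8.5; one-sided results are given where they matter. z(0.975) = 1.960, z(0.95) = 1.645, z(0.99) = 2.326.

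**1. The protocol's 28 per group.** Unpooled z-test, two-sided:

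n = (1.960 + 2.326)² × (0.7×0.3 + 0.2×0.8) / 0.5² = 18.37 × 0.37 / 0.25 = 27.2, so 28. This reproduces.

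The variant matters. Pooled two-sided gives 32 and pooled one-sided gives 27.

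**2. Power for 70% against 20% at 30 per arm, two-sided.**

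- Unpooled: Φ(0.5/√(0.37/30) − 1.960) = Φ(2.542) = 0.994
- Pooled: Φ((0.5 − 1.960×√(2×0.45×0.55/30)) / √(0.37/30)) = Φ(2.235) = 0.987
- Arcsine, using h = 1.055 from step 3: Φ(1.055×√15 − 1.960) = Φ(2.126) = 0.983

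The stated 0.991 lies inside this range.

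**3. Cohen's h.** h = 2·asin(√0.70) − 2·asin(√0.20) = 1.982 − 0.927 = 1.055, not 0.99. An h of about 0.99 belongs to other rates, for example 70% against 22.5% (h = 0.994).

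**4. Power at the stated h = 0.99 with 30 per arm.** 0.99 × √15 = 3.834.

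- Two-sided: Φ(3.834 − 1.960) = Φ(1.874) = 0.970
- One-sided: Φ(3.834 − 1.645) = Φ(2.189) = 0.986

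For power 0.991 at h = 0.99, two-sided, with z(0.991) = 2.366: n = 2 × ((1.960 + 2.366)/0.99)² = 38.2, so 39 per arm. One-sided it is 32.8, so 33.

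**5. The interval 0.89–1.07.**

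- As an interval for power: impossible, because 1.07 exceeds 1.
- As an interval for h at 30 per arm: half-width = 1.96 × √(2/30) = 0.506. That gives 0.48 to 1.50 around 0.99, or 0.55 to 1.56 around 1.055.
- The stated half-width is (1.07 − 0.89)/2 = 0.09. This would need n = 2/(0.09/1.96)² ≈ 950 per arm.
- Its midpoint is 0.98, which is neither 0.99 nor 0.991.

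**6. Dropout.** 28/0.95 = 29.5, so 30 covers 5%. 28/0.90 = 31.1, so 10% would need 32. In the other direction, 30 × 0.90 = 27, below the stated 28. Two-sided power for 70% against 20% at 27 per arm:

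- Unpooled: Φ(0.5/√(0.37/27) − 1.960) = Φ(2.311) = 0.990
- Pooled: Φ((0.5 − 1.960×√(0.495/27)) / √(0.37/27)) = Φ(2.004) = 0.977

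**The case against.** The best defence is that the calculation behind the trial is sound and only its closing sentence is garbled. That largely stands. The 28 per group reproduces, and a power near 0.99 does follow from 70% against 20%. A reader might infer that 0.991 is itself wrong for the sizing rates, or that the trial is underpowered. The documents support neither.

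Sidedness is also open in section 2.5. With a one-sided alpha the gap at h = 0.99 shrinks to 0.986 against 0.991, and the pooled z-test needs only 27 per group, so 28 would suffice there too. It would therefore be wrong to say that 28 holds only for the unpooled test. But no choice of sidedness or test changes h, and none rescues the interval.

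It is tempting to say where 0.991 came from. The two-sided unpooled power at 28 per arm is 0.9916, which rounds to 0.992, while one-sided pooled power at 27 and one-sided arcsine power at 29 both round to 0.991. The protocol also mentions simulation. The source cannot be established, and the point does not need it.

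On dropout, the shortfall arises only towards the upper end of the range, costs little power, and section 2.8.5 plans multiple imputation. Fair, but the protocol itself raised 28 to 30 to allow for dropout, and at 10% that allowance misses its own target. Imputation is not a full answer either: the analysis set requires at least one post-baseline evaluation, and the first scheduled rating-scale assessment after baseline is at week 3.

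One might also question the 20% sham response. The documents give no other sham rate, so that is a separate matter and is not part of this point.

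**Conclusion.** Wrong as written, in one sentence, with no consequence for the sample size. The effect size should read 1.055. The pairing of h = 0.99 with power 0.991 at 30 per arm overstates power by about 2 percentage points two-sided (0.970) and by half a point one-sided (0.986). The interval fits no quantity in the section.

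The dropout allowance covers 5% but not 10%. At 10% the trial would have 27 per arm, with two-sided power of 0.990 (unpooled) or 0.977 (pooled) for the sizing rates.

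These figures rest on the protocol's own 70% and 20%, on normal approximations, and on two-sided testing except where one-sided is stated. On those assumptions power stays high throughout, so this is a correction to what is reported and does not show an inadequate trial.

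**What to change.** Keep N = 60 and rewrite the end of section 2.5:

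- Replace h = 0.99 with h = 1.055.
- Name the z-test variant and state whether alpha is one- or two-sided, consistently with section 2.8.5.
- Restate power for 70% against 20% under that test at 30 per arm and at 27 per arm (10% dropout). Two-sided, this is 0.994 and 0.990 if unpooled, or 0.987 and 0.977 if pooled.
- Say that 30 per group preserves the minimum of 28 at 5% dropout but not at 10%.
- Delete the 95% interval of 0.89–1.07.

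The cost is one reworded paragraph. Recruitment, design and analysis do not change. If the pooled form is named, the stated power becomes slightly less favourable than 0.991.
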